### Design:

The study comprised a multicentre, triple-blind, randomised, controlled, two-arm (1:1) trial. Treatment outcomes will be assessed at baseline, at post-intervention, and at 3, 6 and 12 months follow-up. At the 3 and 6-month follow-up, online self-reported outcome data was collected.

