#### Explorative, secondary other outcomes:

- The Hospital Anxiety and Depression rating scale (HADS) to assess self-reported affective symptoms. It is a 14-item scale with depression subscale and anxiety subscale. Score ranges from 0 to 21, with 0 indicating absence of depression or anxiety and 21 indicating the presence of depression or anxiety. It includes a 7-item 4-point Likert 'depressive symptoms' subscale (0-21) and 7-item 4-point Likert 'Anxiety' subscale (0-21). Both apply a 4 week time interval
- The Short Form Health Survey-36 (SF-36) to assess physical and mental functioning. The SF-36 is widely used a generic measure of health-related quality of life and constitutes well characterised psychometric properties.
- Physical activity recorded over 7 consecutive days by three-axis wrist worn accelerometers (GT9X-BT, Actigraph) will be used to define number of steps and percentage in level of activity (sedentary, light, moderate, vigorous) will be used as measure of physical activity.
- Adverse events classified as serious (led to death, life-threatening, required hospitalization, prolonged hospitalization, led to prolonged or significant disability).

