### Statistical analysis plan

1. **Data source:** Data are derived from nCSP patients with insomnia who participate in this randomised controlled trial. They were evaluated at baseline, at post-intervention and at 3, 6 and 12 months follow-up. The primary outcome is average pain intensity in the last 24h assessed with the BPI.
2. **Analysis objectives:** To investigate the effectiveness of CBTi-BEPM versus BEPM in terms of the above-mentioned primary outcome at 12 months follow-up, and pain-related, sleep related and other secondary exploratory outcomes.
3. **Population:** nCSP patients with insomnia
4. **Endpoints:** Change in outcome measures from baseline to each follow-up point
5. **Covariates:** Sensitivity analyses performed for the primary outcome and all exploratory outcomes by controlling for baseline levels of pain intensity for pain-related outcomes and baseline levels of insomnia severity for sleep-related outcomes. These baseline levels were added to the random-intercept fixed slope linear mixed model analysis as confounding factor.
6. **Handling of missing data:** Analyses are carried out using linear mixed models which can handle missing data.
7. **Statistical methodology:**  

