Descriptive statistics were used to report the demographic variables and baseline characteristics of the participating nCSP patients per intervention group, with means (Standard Deviation [SD], range and Inter Quartile Range [IQR]) for continuous variables and frequency (%) for categorical variables. All analyses were by intention-to-treat, with all participants included in the analysis according to their randomly allocated treatment. All analyses were performed in SPSS 24.0. For average pain intensity (primary outcome) and for all explorative, secondary outcomes, the change between baseline and other time points was calculated:  $\Delta 1 = \text{baseline (T0)} - \text{post-treatment (T1)}$ ;  $\Delta 2 = \text{T0} - \text{3-month follow-up (T2)}$ ;  $\Delta 3 = \text{T0} - \text{6-month follow-up (T3)}$ ; and  $\Delta 4 = \text{T0} - \text{12-month follow-up (T4)}$ . Differences in the change in average pain intensity at 12-month follow-up (primary outcome at primary endpoint) and at the other time points (immediately post-intervention, and at 3- and 6-month follow-up) were analysed using a random-intercept fixed slope linear mixed model (incl. LSD post-hoc analyses), which was applied using an unstructured covariance matrix. Linear mixed models are a likelihood-based estimation procedure whereby likely values for missing data are estimated from information contained in the observed data, resulting in non-biased estimates providing data are missing at random. The model included treatment, time, and treatment\*time as fixed effects together with a random intercept for each patient. Model assumptions were evaluated visually using residual plots. Mean group differences (95% confidence interval) at the different time points and their p-values and effect sizes for the intervention comparisons are reported. Level of significance for the primary outcome was set at  $\alpha .05$ . Effect sizes were calculated as Cohen's d (interpreted as  $>1.3$  = very large;  $.80-1.29$  = large,  $.50-.79$  = medium,  $.20-.49$  = small,  $<.20$

= negligible). The same analysis was used to evaluate the explorative, secondary outcomes at the different time points.

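### Serious adverse events fall under the SAP's change-from-baseline mixed model, which does not fit an event outcome, and no other rule covers them

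*Combined protocol and SAP*

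**What the plan says.** In the protocol's outcome list, the last bullet under "Explorative, secondary other outcomes" is "Adverse events classified as serious (led to death, life-threatening, required hospitalization, prolonged hospitalization, led to prolonged or significant disability". It stands beside the HADS, the SF-36 and accelerometry. The bullet defines seriousness but gives no collection schedule, observation window or summary measure.

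The SAP then sets general rules and makes no exception for this outcome:

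- Item 4 (Endpoints): "Change in outcome measures from baseline to each follow-up point".
- Item 6 (Handling of missing data): "Analyses are carried out using linear mixed models which can handle missing data".
- Item 7 (Statistical methodology): "For average pain intensity (primary outcome) and for all explorative, secondary outcomes, the change between baseline and other time points was calculated", as T0 minus T1, T2, T3 and T4. The changes are modelled with treatment, time and their interaction plus a random intercept, and reported as mean group differences with Cohen's d. The paragraph closes: "The same analysis was used to evaluate the explorative, secondary outcomes at the different time points".

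Item 7 does provide for frequencies and percentages, but only for demographic and baseline variables.

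**The concern.** A score such as the HADS has a value at T0 and at each later visit, so a mean change is meaningful. A serious adverse event is something that happens, or does not, during a period of observation. The natural summary is how many of the people randomised to each arm had one. The SAP's rule produces a difference in mean change and a standardised effect size, neither of which states that number.

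The rule also handles absence badly for this outcome. In a model of change scores, a participant with no record after baseline supplies no row. For a questionnaire that is ordinary missingness. For someone who dies before T1, the absence is caused by the outcome itself, so assuming it is missing at random is not credible.

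This is the only adverse-event outcome the protocol lists, so the trial's formal statement on harm depends on it. The experimental arm includes restriction of time in bed, with a stated lower limit on the sleep window and therapist oversight. A readable comparison of events by arm is what readers will look for.

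**Working it through.** The plan gives no figure for serious adverse events, so there is none to reproduce. The check compares the sections, then adds an illustration and a precision calculation.

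**1. Does the general rule reach this outcome?** The outcome list places serious adverse events in the exploratory secondary class. SAP item 4 defines endpoints as change from baseline, and item 7 extends change scores and the mixed model to all outcomes in that class. Taken as written, the rule applies.

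**2. Does any other rule displace it?** The frequency and percentage sentence in item 7 covers demographic and baseline variables only. The sensitivity analyses add a baseline covariate for pain-related and sleep-related outcomes. The dropout analysis compares baseline data. None gives an event count, observation window, analysis set or table by arm.

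**3. What would the rule return?** This illustration rests on assumptions that are not in the documents:

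- 60 participants per arm (120 randomised 1:1).
- Three experimental participants with an event: one death before T1 and two hospitalisations, first recorded at T2 and T4. No control events.
- A 0/1 indicator at each visit, with T0 = 0 for everyone.
- A random-intercept model with treatment, time and their interaction. The SAP's unstructured covariance was not imposed.

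The true result is 3/60 = 5.0% versus 0/60 = 0%. Because T0 = 0, each change is minus the visit indicator. The participant who died has no row, leaving 120 − 1 = 119 in the model, 59 of them in the experimental arm. Two of the three participants with an event are visible.

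| Visit | Experimental mean change | Control mean change | Difference |
|---|---|---|---|
| T1 | 0 | 0 | 0 |
| T2 | −1/59 = −0.017 | 0 | −0.017 |
| T3 | 0 | 0 | 0 |
| T4 | −1/59 = −0.017 | 0 | −0.017 |

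The control arm has zero variance throughout. At T1 and T3 both arms have zero variance, so Cohen's d would be 0/0. No line of the output says that three participants had an event.

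**4. What would a simple count offer?** The exact (Clopper–Pearson) two-sided 95% upper limit for 0 events in n is 1 − 0.025^(1/n). With n = 60: 1 − 0.025^(1/60) = 0.0596, or 6.0%. Other assumed counts, also exact:

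| Participants with an event | Percentage | 95% CI |
|---|---|---|
| 0/60 | 0% | 0 to 6.0% |
| 1/60 | 1.7% | 0.04% to 8.9% |
| 3/60 | 5.0% | 1.0% to 13.9% |

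These intervals are wide, and a formal test adds little: 3 versus 0 gives a two-sided Fisher p of 0.24, and 5 versus 0 gives 0.057. The table by arm is therefore descriptive, but readers can interpret it directly.

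**The case against.** The strongest reply is that the SAP never names adverse events. Change scores, residual plots and Cohen's d are plainly written for measured scales. A sensible analyst would see that the rule does not suit events and would tabulate them, so this is an omission and not a chosen method. That is probably right as to intention. It does not remove the point. Either the rule applies as written and does not fit, or it does not apply and the only listed adverse-event outcome has no rule. Both readings need the same correction.

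A second reply is that a cumulative 0/1 flag could be carried forward, so that the T4 difference, with its sign reversed, becomes a risk difference. The SAP does not describe that coding. In the illustration it would give 2/59 = 3.4% instead of 3/60 = 5.0%, because the death still supplies no row.

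A reader might infer more than the documents support:

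- **That events are collected only at visits, so any event after a last visit goes unseen.** The Design section says "At the 3 and 6-month follow-up, online self-reported outcome data was collected", but that concerns self-reported outcome data. Nothing states how or when serious events are recorded, and continuous logging is not excluded. The lost death in the illustration follows from the assumed visit-based coding and does not show how this trial collects events.
- **That the anticipated 20% loss to follow-up measures the damage.** A smaller denominator gives a wider interval, but that says nothing about what the mixed model does to events. It also assumes event status is known only for completers.
- **That the trial would wrongly report no safety difference.** No event rate is given, and a rule that fits this poorly may simply not be applied.

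It is also fair to note that the protocol sets a floor on the sleep window on safety grounds and includes the Epworth Sleepiness Scale. Neither replaces a count of serious events.

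**Conclusion.** The point holds as a mismatch between outcome type and stated analysis. It rests on the wording of the outcome list and of SAP items 4, 6 and 7, and not on any assumption about event rates or collection. Followed literally, the SAP would report mean change and Cohen's d for an event with no meaningful baseline. It would not state the number of participants affected, and it would omit anyone with no post-baseline record. It is probably a drafting gap.

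The size of any distortion cannot be stated, because the documents give neither an event rate nor a collection method. The 6.0% upper limit for 0/60 assumes equal arms of 60 and only shows what a count could convey. The primary estimand, the sample size and the efficacy conclusions are untouched. The SAP should still be changed, because its stated rule does not answer the harms question and the replacement costs almost nothing.

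**What to change.** Add to SAP item 7, after the sentence extending the analysis to secondary outcomes, and note the exception in item 4:

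> Serious adverse events are not analysed as change scores or in the mixed model; for each arm we report the number and percentage of all randomised participants with at least one such event from randomisation to the 12-month follow-up, with an exact 95% confidence interval, and the total number of events. Every event known to the trial is counted, whatever its timing relative to visits and whether or not the participant has discontinued, and the number of participants with unknown event status is shown.

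The cost is two sentences and one table. No new follow-up procedure is needed: the rule uses what the trial already knows and discloses what it does not. An estimated risk difference between arms could be added but is optional with few events. Stating how and when events are recorded would also help the reader, since the documents do not say.

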**Randomisation:**

Randomization is computer-generated at the Biostatistics Unit of Ghent University by an independent investigator, uninvolved in any other trial aspects. Block randomisation was used (ratio 1:1) for the two treatment centres (Ghent; Brussels) separately, with stratification for sex (male; female) and dominant pain location (neck; low back). The randomisation is performed by an independent researcher, who places papers indicating group assignment in sequentially numbered, opaque, and sealed envelopes. Concealed allocation is ensured since the independent researcher – who will be the only person with access to the envelopes – writes the initials of the selected participants on the appropriate envelope before opening them.

**Outcome measures:**Primary outcome:

The primary clinical outcome is defined as average pain intensity, assessed using the Brief Pain Inventory (BPI) item 'average pain intensity in the last 24h' evaluated on an 11-point NRS (30% decrease is clinically important).

Explorative, secondary pain-related outcomes:

- BPI worst pain intensity (last 24h) on an 11-point (0–10) numeric rating scale
- BPI least pain intensity (last 24h) on an 11-point (0–10) numeric rating scale
- BPI pain intensity now on an 11-point (0–10) numeric rating scale
- BPI pain severity: the mean of the four pain intensity items
- BPI pain interference: the BPI also evaluates the pain interference related to general activity, walking, work, mood, enjoyment of life, relation with others and sleep on separate 11-point numeric rating scales.
- The Central Sensitisation Inventory (CSI; cut-off value of 40/100 to indicate the presence of central sensitization-related symptoms) to assess symptoms of central sensitisation. The CSI uses 25 statements related to current health symptoms, indicative of central sensitization (scored on a five-point Likert scale ranging from zero to four).

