Sensitivity analyses were performed using the same analysis, including the baseline level of average pain intensity (for all pain-related outcomes) and the baseline level of insomnia severity (for sleep-related outcomes) as confounding factor. The analysis of dropout and loss-to-follow-up was conducted by categorizing the entire cohort into two subsets, distinguished by their adherence or discontinuation from the trial (which also included loss-to-follow-up). Comparative assessment of baseline characteristics and data between the two groups was accomplished utilizing a t-test or its non-parametric equivalent.

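### The primary model compares unadjusted change scores and leaves baseline pain to a sensitivity analysis; this is valid but generally less precise, and adjustment costs nothing

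*Combined protocol and SAP*

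**What the plan says.** SAP item 4 (Endpoints) defines the endpoint as "Change in outcome measures from baseline to each follow-up point". Item 7 (Statistical methodology) states that "the change between baseline and other time points was calculated". It forms four differences, baseline minus each follow-up, and names the 12-month difference in average pain as the primary outcome at the primary endpoint. On the fixed effects it says "The model included treatment, time, and treatment"-by-time interaction, together with a random intercept per patient. Baseline pain is not among them.

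Baseline pain appears in item 5 (Covariates), which lists only "Sensitivity analyses performed for the primary outcome and all exploratory outcomes by controlling for baseline levels of pain intensity" (insomnia severity takes that place for the sleep outcomes). Item 5 adds: "These baseline levels were added to the random-intercept fixed slope linear mixed model analysis as confounding factor". The last part of item 7 repeats this, again as a sensitivity analysis and without a baseline-by-time term. The SAP gives no reason for leaving baseline out of the primary model.

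Under Randomisation, the protocol stratifies by sex and dominant pain location within each centre. Baseline pain is not a stratification factor, so the design does not balance it directly.

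**The concern.** An unadjusted change score subtracts the whole baseline value, which fixes the slope of follow-up on baseline at 1. The efficient slope is rho × SD4/SD0, where SD0 and SD4 are the SDs at baseline and 12 months. With equal SDs this is rho, which is below 1. The change score then over-corrects: patients with high baseline pain tend to show more improvement through regression to the mean, and so does an arm that happens to start with more pain.

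Two things are at stake. The trial's single primary test may be less precise than the data allow. The headline estimate also depends on how baseline pain happened to fall between arms in a trial of 60 per arm. The covariate that addresses both is already collected and already modelled, but only in the secondary role.

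**Working it through.** **Inputs from the documents.** N = 120, 1:1 allocation, f = 0.25 (d = 0.50 for two groups), alpha .05, power .80, 20% loss at one year (protocol, Sample size calculation and Design). Completers: 120 × 0.8 = 96, or 48 per arm.

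**Inputs not in the documents (assumptions).** The baseline-to-12-month correlation rho is taken as 0.3 to 0.7. SD0 and SD4 are first taken as equal, then varied. d = 0.50 is taken on the 12-month SD.

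**The plan's own figure.** N = 120 can be reproduced only with inputs that the text does not state. A repeated-measures between-groups F-test with 3 measurements and correlation 0.6 gives 96, and 96/0.8 = 120. With 2 measurements and correlation 0.5 it gives 98, and 98/0.8 = 122.5, so 123. A plain two-group F-test gives 128, and 128/0.8 = 160. The text therefore does not show whether baseline adjustment was assumed.

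**Which response variable.** If the model were fitted to raw scores including baseline, with an unconstrained group difference at baseline, the 12-month interaction contrast with complete data would still be an unadjusted difference in change. The comparison below applies under either reading.

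**Variance, equal SDs (SD = 1).**
- Change score: 2(1 − rho)
- Baseline-adjusted: 1 − rho²
- Ratio, adjusted to change: (1 − rho²) / [2(1 − rho)] = (1 + rho)/2

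**Power.** Two-sided two-sample noncentral t, 48 per arm, noncentrality (0.5/√variance) × √(48/2).

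| rho | Var. change | Var. adjusted | Ratio | Noncentrality | Power |
|---|---|---|---|---|---|
| 0.3 | 1.40 | 0.91 | 0.65 | 2.07 → 2.57 | 54% → 72% |
| 0.5 | 1.00 | 0.75 | 0.75 | 2.45 → 2.83 | 68% → 80% |
| 0.7 | 0.60 | 0.51 | 0.85 | 3.16 → 3.43 | 88% → 92% |

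Simulation of 20,000 trials per rho (48 per arm) gave variance ratios of 0.66, 0.77 and 0.86. These figures treat the 12-month comparison alone. They include no borrowing from earlier visits, because the documents give no interim retention.

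**Unequal SDs.** Let k = SD4/SD0 and SD4 = 1. The change-score variance is 1 + 1/k² − 2·rho/k; the adjusted variance stays 1 − rho².
- k = 1.2: change-score variances 1.19, 0.86 and 0.53; ratios 0.76, 0.87 and 0.97; power 60% → 72%, 74% → 80%, 92% → 92%.
- k = 0.8: change-score variances 1.81, 1.31 and 0.81; ratios 0.50, 0.57 and 0.63.

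**Sensitivity to baseline imbalance.** With equal SDs, a baseline difference D shifts the change-score effect by (1 − rho) × D. For D = 0.5 NRS and rho 0.5 the shift is 0.5 × 0.5 = 0.25 NRS. In SD units with 60 per arm, the standard error of a chance difference is √(2/60) = 0.18, and 1.96 standard errors is 0.36. That shifts the effect by 0.25, 0.18 or 0.11 SD at rho 0.3, 0.5 or 0.7. In the simulation the change-score estimate moved with the imbalance at slopes of 0.71, 0.49 and 0.30 in absolute value. The adjusted estimate had slopes of about zero. Averaged over all simulated trials, both estimates were centred on the true effect.

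**The case against.** The strongest reply is that nothing here is invalid. Allocation is concealed, stratified and 1:1, so the change-score estimate is unbiased over randomisations and type I error holds. This stands. A reader might infer that the primary estimate is biased; the documents do not support that. What is shown is a shift conditional on an imbalance that happens to occur.

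Second, the size of the gain rests on quantities that the documents do not give. This also stands. At k = 1.2 and rho 0.7 the two analyses are nearly equivalent. The direction is firmer: adjustment is never less efficient asymptotically.

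Third, a reader might infer that adjustment repairs a power shortfall at n = 120. That is not established. The sample size text does not say which SD standardises f = 0.25. If it is the change-score SD, change-score power is 68% at every rho and adjustment gives 85%, 80% and 75% at rho 0.3, 0.5 and 0.7. If it is the 12-month SD, the change score already has 88% at rho 0.7. Neither shows that N is wrong.

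Fourth, the adjusted model is already prespecified for the primary outcome, and adding baseline to a change-score model gives the same treatment effect as adjusting the follow-up score. Both estimates will therefore exist. This limits the harm but does not remove it, because the generally less precise estimate is the one that carries the primary conclusion. The planned adjusted model also forces one baseline slope across all follow-ups, which may not suit 12 months if the correlation with baseline weakens over time.

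**Conclusion.** The point holds as one of efficiency and robustness, not validity. The adjusted variance is 0.65 to 0.85 of the change-score variance for rho 0.3 to 0.7 with equal SDs, and 0.76 to 0.97 if the SD is 1.2 times larger at 12 months. The power gains of 18, 12 and 4 percentage points at rho 0.3, 0.5 and 0.7 also require d = 0.5 to be on the 12-month SD and 96 completers. The correlation, the SDs and the standardiser are all assumptions. The plan should be changed because the improvement is free, but a trial analysed as written would still give a valid primary test.

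**What to change.** Make the baseline-adjusted model primary. Either model the four follow-up scores with fixed effects for treatment, time, treatment-by-time, baseline pain and baseline-by-time, or use a constrained longitudinal model with all five visits as responses and a common baseline mean. Read the treatment effect from the 12-month contrast. Keep the unadjusted change-score model as the sensitivity analysis. Describe baseline pain as a prognostic covariate; in a randomised comparison it is not a confounder.

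The cost is a revision of SAP items 5 and 7, with no new data. Timing matters: the analysis section is written largely in the past tense, while the Study population section still speaks of future recruitment, so the documents do not show whether outcome data have been seen. If the change precedes sight of unblinded outcome data, it is a simple amendment. If not, label the adjusted analysis post hoc and report both.

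### The primary model pairs a random intercept with an unstructured matrix and does not say which matrix is meant: one reading is redundant, the other may misstate the 12-month standard error

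*Combined protocol and SAP*

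**What the plan says.** Item 1 of the SAP sets out five assessments: "They were evaluated at baseline, at post-intervention and at 3, 6 and 12 months follow-up". Under item 7, for the primary outcome and all others, "the change between baseline and other time points was calculated", which yields four change scores. The primary comparison is the group difference in the last of these, at 12 months.

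The same item says that the differences in change "were analysed using a random-intercept fixed slope linear mixed model", "which was applied using an unstructured covariance matrix". Treatment, time and their interaction enter "as fixed effects together with a random intercept for each patient". Item 5 carries the model into the sensitivity analyses: "These baseline levels were added to the random-intercept fixed slope linear mixed model analysis as confounding factor".

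The random intercept is thus named three times and the unstructured matrix once. The SAP does not say whether the latter describes the random effects or the residuals. It names no separate residual structure, no degrees-of-freedom method and no fallback for non-convergence. The software is SPSS 24.0.

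**The concern.** A random intercept and an unstructured residual matrix are two ways of describing the same within-patient dependence. Both together are more than the data can separate. If the unstructured matrix belongs to the random effects instead, the label does nothing, because a single random intercept has only one variance. Two analysts could follow the text faithfully and report different 12-month SEs, confidence intervals and p-values.

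Three features of the plan make this matter for the primary result.

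- The response is change from baseline. With equal raw SDs its variance is 2σ²(1 − ρ), where ρ is the correlation with baseline. It therefore grows if ρ falls with time, and the primary contrast is at the latest visit.
- The Design section singles out 3 and 6 months for online self-report, so the mode of collection may differ between visits.
- The sample size paragraph expects 20% loss by one year, and SAP item 6 relies on this model alone for missing data. The covariance decides how much earlier visits count for patients missing at 12 months.

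**Working it through.** **Inputs from the documents.** Five visits and four change scores (SAP items 1 and 7); one random intercept per patient; 120 patients allocated 1:1, so 60 per arm; 20% loss; α = 0.05 (two-sided assumed). The documents state no SE and no SD or correlation by visit, so there is no figure of the plan's own to reproduce, and every magnitude below rests on assumed values.

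**Reading (a): the residual matrix is unstructured.**

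1. Distinct variances and covariances of k repeated measures: k(k + 1)/2. For k = 4 this is 10; for k = 5 (baseline kept as a response) it is 15.
2. Parameters: 10 + 1 = 11, or 15 + 1 = 16. There is one too many, so the intercept variance is not identifiable. The total covariance still is.
3. Check on one simulated data set (120 patients, four change scores, 20% dropout). Fixing the intercept variance at 0, 0.47, 0.95 or 1.50 gave the same −2 REML log-likelihood (848.053) and the same 12-month SE (0.40887) each time. Free fits from three starting points gave intercept variances of 0.18, 0.62 and 1.38, but the same estimate (−0.647) and SE (0.409). The unstructured model without a random intercept also gave 0.409.

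**Reading (b): the random-effects matrix is unstructured.**

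1. It is a single variance. With independent, equal-variance residuals (assumed) the model has two covariance parameters, which is compound symmetry.
2. On the same data set the 12-month SE was 0.355, and 0.355/0.409 = 0.87, so it is 13% smaller. Holding the estimate at −0.647 for illustration, z = 0.647/0.409 = 1.58 (p about 0.11) or 0.647/0.355 = 1.82 (p about 0.07).
3. With complete data, SE ratio r = √(mean of the four visit variances ÷ 12-month variance), and type I error = 2Φ(−1.96 r). From raw scores, the variance of change k is σ₀² + σₖ² − 2ρₖσ₀σₖ.

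| Assumed setting, complete data | Ratio r | Type I error |
|---|---|---|
| Equal raw SDs, all correlations 0.5 | 1.00 | 5.0% |
| Raw SDs 1.6/2.1/2.2/2.3/2.4, correlations 0.5 | 0.95 | 6.3% |
| Change SDs 2.0/2.1/2.2/2.3 | √(4.635/5.29) = 0.936 | 6.7% |
| Equal raw SDs, correlation 0.65 − 0.05 per visit apart | 0.93 | 6.9% |
| That decay with the rising raw SDs above | 0.89 | 8.0% |
| Raw SD 2, correlation 0.7 per visit: change variances 2.40/4.08/5.26/6.08 | √(4.45/6.08) = 0.86 | 9.3% |
| Change SDs 1.8/2.0/2.2/2.5 | √(4.5825/6.25) = 0.856 | 9.3% |
| Raw SDs 2.0/2.2/2.1/2.0/1.9, correlation with baseline rising 0.42 to 0.63: change variances 5.14/4.29/3.52/2.82 | √(3.945/2.822) = 1.18 | 2.0% |

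4. With 20% dropout by 12 months (1,200 simulated trials per setting, 60 per arm, no true effect), the two change-SD settings gave 8.8% and 10.8%. The Monte Carlo standard error is √(0.088 × 0.912/1200) = 0.8 and √(0.108 × 0.892/1200) = 0.9 percentage points. Equal SDs with decaying correlation gave about 6.7%. SDs falling from 2.4 to 2.0 gave an SE about 5% too large. These rates also depend on the correlation assumed between visits.
5. If raw scores at all five visits are modelled instead, the complete-data ratio runs from 0.80 (type I error 11.9%) to 1.13 (2.7%).

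**The case against.** The strongest reply is that this is a gap in reporting with no shown effect on inference. Under reading (a) the redundancy touches only a nuisance parameter, so dropping the intercept changes neither estimate nor SE. That stands. A reader might infer that the primary model as a whole cannot be estimated, or that it will probably fail to converge. The check does not support either: the treatment contrast is identified, and all three free fits reached the same answer. A Hessian or convergence warning is a risk and was not shown to be likely.

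Reading (b) needs an assumption that the SAP does not state. A random intercept with visit-specific residual variances is a third possibility, and it removes most of the error. With complete data and correlations either exchangeable at 0.6 or decaying at 0.7 or 0.8 per visit, change SDs 2.0/2.1/2.2/2.3 give ratios of 0.97 to 1.05 (type I error 4.0% to 5.7%), and 1.8/2.0/2.2/2.5 give 0.93 to 1.01 (4.8% to 6.8%). This also stands, and it shows how much turns on a structure that the plan leaves open.

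A reader might further infer that the plan gives a wrong 12-month SE, or an inflated type I error. The documents do not support that. If compound symmetry is true, the SE is right; if not, the error can go either way. With complete data and equal change-score SDs the ratio is 1.00 even when the correlation between visits decays.

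The plan does commit to inspecting residual plots. That is partial mitigation, because no action is tied to what they show and they do not settle which model is fitted.

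**Conclusion.** The point holds as a should-fix. The covariance model for the primary analysis cannot be reproduced from the text. One reading carries a redundant parameter, with no effect on the 12-month result if the fit converges. The other, if residuals are independent with equal variance, places an untested compound-symmetry restriction on the primary SE.

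Under that second reading, type I error on change scores ranged from about 2% to 11% over the assumed settings, and reached about 12% in one setting with raw scores. Neither the size nor the direction for this trial can be fixed from the documents. It is still more than missing detail, because the choice can move the primary p-value, 20% loss is expected, and a standard specification remains valid whether or not variances and correlations differ by visit.

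**What to change.** Replace the covariance wording in SAP item 7 with a complete specification for the primary analysis: REML; time as categorical; unstructured residual covariance within patient across the four post-baseline visits (SPSS MIXED with /REPEATED and COVTYPE(UN)); no random intercept; Satterthwaite degrees of freedom. Add a fixed fallback order for non-convergence, for example heterogeneous Toeplitz, then heterogeneous AR(1). Other orders would also serve; what matters is that the order is set in advance. Bring the random-intercept wording in item 5 into line.

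Parts of the SAP are written in the past tense. If the analysis has already been run, state which model was fitted and report this one as well.

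The cost is one sentence of SAP text, one change of syntax, and 10 covariance parameters instead of 2 under compound symmetry. With 120 patients, or 120 × 0.8 = 96 at 12 months, and four visits, that is affordable.
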